## Safety

The adverse events (AEs) will be self-declared by the patient through the patient logbook. This will be collected at the 3-month post-operative visit. Patients will be questioned about AEs by the investigators.

A telephone call by the clinical research assistant (CRA) will be made 1 month after surgery to check that furosemide is well tolerated once the patient has returned home and also to check for the presence of a post-operative UTI or any other AEs.

## Participant timeline

Duration of participation will be 3 months (± 2 weeks) for each patient. The time schedule of enrolment and visits is in Fig. 1 and Table 2.

**Fig. 1 Fig1:**
[figure not shown]
Participant timeline

**Table 2 Tab2:** Schedule of enrolment, interventions, and assessments

Timepoint	Inclusion	*− 7 days*	*− 48/72 h*	*D0*	*M1*	*M2*	*M3*
**Before intervention**							
Check inclusion and non-inclusion criteria	X						
Patient information	X						
Signature of consent form	X						
Physical examination	X						
Vital signs with blood pressure monitoring	X						
Phone call		X					
ECBU^a^		X					
Blood test^b^			X				
**Intervention**							
Urinary pregnancy test				X			
Flexible ureteroscopy				X			
Randomization				X			
Furosemide				X			
Clinical examination				X^c^			
Blood pressure				X^c^			
Cardiac frequency				X^c^			
**After intervention**							
Post-operative visit^d^				X			
Follow-up book					X	X	X
Phone call					X	X	
Low dose abdomino-pelvic CT scan							X
**Safety evaluation**							
Adverse events (serious or not)	X	X	X	X	X	X	X

^a^An ECBU may be performed in the event of postoperative urinary tract infection symptoms

^b^Blood test includes a blood count and platelet count, creatinine levels, creatinine clearance, and a blood ionogram. Other parameters may be added at the anesthetist’s request, as is standard practice

^c^Monitoring of 5 h to 7.5 h

^d^Clinical examination, blood pressure, cardiac frequency, evaluation of pain

The patient will be recruited by the urologists on the day when the indication to perform a fURS for the destruction of kidney stones is established. Initial information will be given by the urologist during this consultation. An appointment will be made with a CRA following this consultation to discuss the study in more detail and answer any questions the patient may have, particularly regarding logistical aspects. After this interview with the CRA, the patient will see the urologist again to sign his consent if he agrees to take part in the study, prior to any investigation.

The patient will be called for his/her anesthesia consultation in the month prior to the procedure, as is done in current practice. As it is usually done, an ECBU will be done 1 week before the surgery [14]. A blood ionogram and creatinine will be necessary before inclusion in the study to verify the absence of contra-indications, particularly to furosemide. This blood test should be performed 48–72 h before the surgical procedure in order to be as close as possible to the furosemide injection, if applicable.

The CRA will contact the patient by phone 1 week before the surgery to remind him/her of the necessity to perform the biological check-up 48–72 h before the surgery to verify his/her eligibility for the furosemide injection if necessary.

A urinary pregnancy test will be performed for women of childbearing age on the morning of the procedure.

The randomization will be done at the end of the fURS, if the destruction of the kidney stone is macroscopically complete. The anesthesia team injects furosemide or not, depending on the randomization of the patient.

At post-operative visit, careful monitoring will be carried out in the recovery room by the anesthetic nurses for about 2 h after the operation.

The half-life of furosemide is 1 h to 1.5 h after injection. Considering that the product is completely eliminated from the body after 5 half-lives, a monitoring of 5 h to 7.5 h will be required to ensure optimal monitoring of patients after their injection, which corresponds to the postoperative monitoring in routine practice (in conventional or ambulatory units).

Evaluation of pain will also be assessed by nurses during hospitalization. Pain will be assessed using a numerical pain scale ranging from 0 to 10. This will be done at three time points: in the recovery room, in the service, and at the discharge.

The patient will be followed up for 3 months (± 2 weeks), after the surgery. Patients will use a follow-up book to carry out a self-assessment in particular on the UTI. As usually, patients should consult their general practitioner in the event of sign of infection. However, only the combination of some of these symptoms will be synonymous with a UTI, requiring the expertise of a general practitioner or urologist to distinguish between a real UTI and just the postoperative symptoms caused by the procedure performed in the excretory tract, corresponding to the healing of the urinary mucosa. The ECBU should only be carried out at the request of a doctor (general practitioner or urologist).

A phone call will be performed 1 month after the procedure. We will collect the potential event: fever > 38.5 °C, chills, clinicals symptoms, call or consultation with general practitioner or urologist within 30 days of surgery, ECBU performed within 30 days of surgery, antibiotics within 30 days of surgery. All adverse events presented by the patient since the intervention will be collected.

The patient will have to perform his/her low dose abdomino-pelvic CT scan without injection at 3 months after the operation (± 2 weeks).

We scheduled another phone call by the CRA at about 2 months post-operatively to remind the patient to have his non-injected low-dose abdominal-pelvic CT scan at 3 months (± 2 weeks).

The results of the CT scan should be brought back at the 3-month follow-up consultation with his/her referring urologist. The CT scan data will be interpreted by the urologist and retrieved for an anonymous reading by 2 radiologists in a blind process.

We will also collect the occurrence of UTI in the first post-operation month or other complications, using the patient’s memory and the participant diary noting information.

The CT scans will be collected by the CRA and will be recorded on a dedicated and anonymized platform in order to allow blind evaluation of the images by the 2 specialist radiologists.

A metabolic work-up (blood test, urine test based on a morning sample and 24-h urine collection) is essential for all patients with lithiasis. If the work-up has not already been carried out in the patient’s history of lithiasis, it should be performed postoperatively [14].

At the end of the study, the patient will continue the usual follow-up with his/her referring urologist.

The overview of the study is summarized in Fig. 1 and in Table 2.

## Sample size

The proportion of stone-free patients at 3 months is expected to be 95% in the furosemide group, as compared to 85% in the control group. Indeed, in the literature, the stone-free rate is estimated at 85% [16]. We hypothesize that our treatment will increase this percentage by 10% to have an impact in current. Considering a two-sided type I error level of 5% and a power of 90%, we need to randomize 374 patients.

Because patients will be pre-included, and randomized only at the end of the surgical procedure, we plan to include 416 patients, thus considering that 10 % of them will not be randomized.

## Recruitment

The patient will be recruited by the urologists the day where the indication to perform a fURS for kidney stone destruction is established.

## Methods: assignment of interventions

### Allocation

#### Sequence generation and allocation concealment mechanism

We will use a computer-generated randomization schedule performed by an independent statistician not otherwise involved in patient recruitment or follow-up. Randomization will be stratified by use of double J stent (yes/no), localization of the stone (inferior calix/other), and complete dusting (yes/no). We will use permuted blocks, and block sizes will not be disclosed to the study investigators to ensure concealment.

Randomization procedure will be centralized via a web-based interactive response system (CSonline) managed by the biometrical unit of the Tours University Hospital, thus ensuring allocation concealment.

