## Abstract

**Background:**

Lithiasis is a common and recurrent disease. Flexible ureteroscopy (fURS) is the cornerstone of laser treatment of kidney stones. Kidney stones destruction requires its laser pulverization into small fragments in order to remove them through the ureter or improve their spontaneous expulsion along the urinary tract. However, most of the time, all the micro-fragments and dust created cannot be extracted using our surgical tools and may stay intra-renally at the end of the procedure. Adjuvant treatments (such as forced diuresis, inversion or mechanical pressure) were previously described to improve the expulsion of stone fragments after extra-corporeal shock wave lithotripsy. Nevertheless, the impact of adjuvant treatment after fURS remains unclear and mainly theoretical.

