### Eligibility criteria

#### Inclusion criteria

Males or females aged 18 to 80 years, with the need to perform a fURS with destruction of the kidney stones with laser for a stones of less than 3 cm, were included.

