## Outcomes

### Primary outcome

The stone-free rate at 3 months of the fURS for renal stone laser destruction will to be evaluated on the low dose abdomino-pelvic CT scan. A centralized review of the images will be performed by two specialized radiologists, in a blinded and crossed way to allow a homogenization of the results.

It was decided to carry out an abdominopelvic CT scan, which is more radiant than a renal ultrasound scan, as this examination is not operator-dependent and can therefore be reviewed by the referring urologist, as well as by several specialized radiologists, to ensure optimal analysis. It was therefore decided to use “low dose” abdominopelvic scans, guaranteeing minimal irradiation (irradiation comparable to a standard X-ray, i.e., 6 times less than a conventional scan), while maintaining optimal analysis of our endpoint [13].

We have designated as “stone-free” patients for whom no calculi were found on follow-up imaging but also if the residual fragments were less than 4 mm [9, 14], as described in the current literature.

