#### Implementation

Randomization will be performed in the operating room, if the destruction of the stone has been macroscopically complete. Participants will be randomly assigned to experimental group (injection of furosemide) or to control group with a 1:1 ratio allocation. The allocating sequence will be implemented by means of an electronic case report form (e-CRF): once a patient is included.

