#### Statistical analysis of the primary outcome

Proportion of stone-free patients at 3 months will be compared between the experimental and the control groups using a logistic regression in which stratification variables will be included. The intervention effect will then be expressed as an odds ratio. In agreement with the CONSORT guidelines, the inter-group difference and its 95% confidence interval will also be estimated. For that, a linear model using an identity link function will be estimated. Missing data will be managed using a multiple imputation approach.

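### Pre-operative stone size must be assessed for every patient at entry but is not named as a covariate in the primary model; prespecifying it costs almost nothing and brings a modest gain at most

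*Protocol article*

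**What the plan says.** All references are to the protocol article.

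- **Sequence generation and allocation concealment mechanism:** "Randomization will be stratified by use of double J stent (yes/no), localization of the stone (inferior calix/other), and complete dusting (yes/no". Stone size is not among the three factors.
- **Inclusion criteria:** patients enter "with the need to perform a fURS with destruction of the kidney stones with laser for a stones of less than 3 cm". There is an upper limit on size and no lower one.
- **Primary outcome:** a patient counts as stone-free if no calculus is seen, but also "if the residual fragments were less than 4 mm".
- **Statistical analysis of the primary outcome:** the arms are compared "using a logistic regression in which stratification variables will be included". The effect is reported as an odds ratio, and a linear model with an identity link supplies the difference in proportions. No covariate beyond the stratification variables is named.
- **Background and rational:** stone size, location and density are said to bear on the choice of treatment. Nothing is said about size predicting residual fragments after flexible ureteroscopy.
- **Implementation:** "Randomization will be performed in the operating room, if the destruction of the stone has been macroscopically complete".

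**The concern.** Size has to be assessed before entry, so a baseline value should be available for every randomised patient at little or no extra effort. The endpoint is itself a size threshold on what is left in the kidney. It is reasonable to expect that patients who start with a larger stone are more likely to keep a fragment of 4 mm or more. If so, size explains part of the variation in outcome, and a model that omits it gives up some power.

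What is at stake is efficiency, and the credibility of the result should the arms happen to differ in stone burden. Validity is not at stake, because randomisation protects the comparison whether or not size is in the model.

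**Working it through.** **1. The plan's own sample size.** Inputs from the Sample size section: 85% vs 95%, two-sided 5%, 90% power. Allocation is 1:1 (Implementation). With pooled variance and no continuity correction:

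n per arm = [1.960 × √(2 × 0.90 × 0.10) + 1.282 × √(0.85 × 0.15 + 0.95 × 0.05)]² / 0.10²
= (0.8315 + 0.5361)² / 0.01 = 187.05

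That is 374 in total (376 if each arm is rounded up). Power at 187 per arm is 89.99%. Inclusions: 374 / 0.90 = 415.6, so 416. Both stated figures reproduce, and adding a covariate changes neither.

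**2. Expected failures.** 187 × 0.15 + 187 × 0.05 = 28.05 + 9.35 = 37.4. With treatment and three binary factors as main effects there are 4 terms besides the intercept, so 37.4 / 4 ≈ 9.4 failures per term. Adding size gives 37.4 / 5 ≈ 7.5.

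**3. Power with and without size.** The documents give no association between size and outcome, so it is an assumption, varied over a range. Trials of 187 per arm were simulated with marginal rates of 85% and 95% and a normal size covariate. Each was analysed by logistic regression on treatment alone and on treatment plus size, with 2,500 trials per scenario:

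| Assumed odds ratio for failure per SD of size | Power without size | Power with size | Change (points) |
|---|---|---|---|
| 1.0 | 91.3% | 90.9% | −0.4 |
| 1.5 | 91.4% | 91.5% | +0.1 |
| 2.0 | 90.8% | 91.5% | +0.7 |
| 3.0 | 91.6% | 94.8% | +3.2 |

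The simulation error of a single power figure is √(0.91 × 0.09 / 2500) ≈ 0.6 points, so the first two rows show no change. Two further sets of runs under the same assumptions gave 91.3% to 92.7% and 90.9% to 91.7% at an odds ratio of 2, and 91.2% to 94.0% and 91.0% to 93.4% at 3. Together the gain is 0.7 to 1.4 points at 2 and 2.4 to 3.2 points at 3.

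The three stratification factors were not simulated. If any of them is correlated with size, part of this gain is already in the planned model.

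**4. Type I error.** With no treatment effect, rejection rates in the 2,500-trial runs were 4.7 to 5.0% without size and 4.7 to 5.2% with it.

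**5. Chance imbalance.** The standard error of the standardised difference in mean size is √(2/187) = 0.103, so its 95% range is ±0.20 SD. An imbalance beyond 0.2 SD in either direction has a probability of about 5%. At an imbalance of 0.2 SD, the unadjusted difference in stone-free rates shifts by 1.7 points at an assumed odds ratio of 2 and 2.4 points at 3. The standard error of the planned comparison is √(0.175 / 187) = 3.1 points, so either shift is smaller than one standard error.

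**The case against.** The case against has four parts, and most of it stands.

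*The protocol does not exclude other covariates.* It says the stratification variables will be included, not that nothing else will be. Further covariates are often fixed in an analysis plan, which is not shown. So this is a recommendation about what to prespecify, not a contradiction or a fault in the text.

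*The prognostic role of size is not in the documents.* A reader might infer from the Background that size drives residual fragments, but that sentence concerns the choice of treatment. Randomising only after macroscopically complete destruction may also weaken any link. The strength of association therefore remains an assumption, and at the weak end of the range there is no gain.

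*Chance imbalance is not bias.* A reader might take the 1.7 to 2.4 point shift for a spurious effect. It is ordinary sampling variation, equally likely in either direction and already covered by the test and the confidence interval.

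*The gain is not free precision.* In logistic regression a prognostic covariate does not shrink the standard error of the log odds ratio. Power rises because the conditional effect lies further from the null. One more parameter is also spent on a limited number of failures.

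A separate and stronger reading concerns the third stratification factor. Because patients are randomised only after macroscopically complete destruction, a reader might infer that complete dusting (yes/no) repeats that condition and should be replaced. The documents do not support this. The Abstract's Background says: "Kidney stones destruction requires its laser pulverization into small fragments in order to remove them through the ureter or improve their spontaneous expulsion". A stone can thus be fully destroyed with its fragments removed and not wholly dusted, so both levels can hold eligible patients. At most, the protocol could clarify how the two terms differ.

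**Conclusion.** The point holds as a modest improvement. Pre-operative stone size must be assessed for every patient, is plausibly related to an endpoint defined by fragment size, and is not named in the primary model. Adjusting for it would add about 0 points of power at an assumed odds ratio per SD of 1 to 1.5, about 1 point at 2, and about 2 to 3 points at 3. Those odds ratios are assumptions, and the stratification factors were left out of the simulation. Omitting size neither biases the randomised comparison nor inflates type I error, and the sample size of 374 randomised and 416 included is unaffected.

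**What to change.** Prespecify pre-operative stone size as a continuous covariate, in addition to the stratification variables, in both the primary logistic model and the identity-link model for the risk difference. Three details should be settled with it:

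- State which measure is used when there are several stones (largest diameter or cumulative), and record the value itself, not just that it is under 3 cm.
- Include size in the multiple imputation model so that it matches the analysis model.
- If the identity-link model is fitted as binomial, name a fallback such as a standardised risk difference from the logistic model, since a continuous covariate can push fitted values above 1 when rates are near 95%.

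The cost is one covariate and one parameter on about 37 expected failures. The odds ratio also becomes conditional on size as well as on the strata. Sample size, stratification and the randomisation screen need no change. The Trial status section reports that no patient had been included. The covariate should in any case be fixed before outcomes are examined by arm. Optionally, one sentence could explain how complete dusting differs from macroscopically complete destruction.

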#### Implementation

Randomization will be performed in the operating room, if the destruction of the stone has been macroscopically complete. Participants will be randomly assigned to experimental group (injection of furosemide) or to control group with a 1:1 ratio allocation. The allocating sequence will be implemented by means of an electronic case report form (e-CRF): once a patient is included.

### Blinding

We plan a pragmatic trial, and we deliberately decided not to use a placebo, to make it much easier to conduct. There is no risk of bias, neither for the performance bias (since the intervention consists in only one injection) nor for the detection bias (since the primary outcome will be centrally assessed, by blinded experts). Therefore, we consider a placebo as useless.

In the end, in the present trial:Patients will be blinded: they will not be informed of their allocation at the end of the surgeryUrologists and anesthesiologists will not be blinded. Indeed, depending of the organization, randomization will be performed either by the urologist or the anesthesiologist or by a nurse. We considered that modifying this organization may be a source of burden, without real advantage. So, the care provider (urologist) is not expected to be blindedRadiologists who assess CT scans (i.e., outcome assessor) will be blinded

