## Interventions

The experimental group will receive intravenous furosemide 40 mg, after the end of the surgical procedure, when the ureteroscope is removed from the renal cavities; the anesthetist or the anesthetist’s nurse will inject the experimental treatment. Furosemide 40 mg diluted in 50 mL NaCl 0.9% will be administered as a single slow (over 10 min) intravenous injection.

In the event of poor tolerance during the 10 min slow intravenous injection, this may be stopped at the discretion of the anesthetic team.

The bottles of furosemide are dedicated to the study and supplied by the sponsor. The furosemide prescription will be issued via a nominative prescription obtained from EnnovClinical (e-CRF) after randomization. The department will attach the two detachable labels from the ampoules used, send the original to the pharmacy, and keep a copy in the patient file.

After discussions between urologists, anesthetists, nephrologists and the pharmacovigilance department at Tours University Hospital, we decided to propose a dose of 40 mg of furosemide [12]. Furosemide is an old drug whose side effects are well known and controlled. Dosages of 20 or 40 mg are very low doses of furosemide. Some patients may take 500 mg of furosemide a day. Undesirable effects are therefore considerably lower for dosages of 20 and 40 mg. As part of a pragmatic study looking for a significant improvement in stone evacuation and the stone-free rate, we felt that the 40 mg dosage was preferable, as it could possibly demonstrate a difference that was not visible with 20 mg furosemide, without increasing the risk of complications associated with the drug. As this was the first study to assess the impact of forced diuresis on stone-free levels after fURS for laser destruction of kidney stones, we felt it was important to take every opportunity to find a significant difference, if any.

Treatment must not be administrated in rapid IV injection. Indeed, we chose to carry out a slow injection because the fast injection of furosemide can involve an ototoxicity being able to go until the temporary or final surdity. This risk increases with the dosage used.

The control group will receive standard of care corresponding to the performance of a fURS without injection of furosemide or other drugs.

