#### Statistical analysis of secondary outcomes

Proportion of patients with post-operative UTI within 30 days after surgery will be compared between randomization groups using the same approach as for the analysis of the primary outcome.

Visual numerical scale of pain in the recovery room, in the service, and at discharge will be analyzed using a mixed model. Proportion of patients who received opioids will be compared between randomization groups using the same approach as the one use for the analysis of the primary outcome.

Analysis of the occurrence of furosemide-related events will be descriptive.

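### The statement that there is no risk of bias is supported only for detection bias on the blinded CT reading. It does not cover UTI, opioid use or investigator-elicited adverse events, and the stated safety analysis rests on an undefined term

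*Protocol article*

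**What the plan says.** All references are to the protocol article.

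- **Blinding.** The authors write "we deliberately decided not to use a placebo, to make it much easier to conduct". They then state "There is no risk of bias, neither for the performance bias (since the intervention consists in only one injection) nor for the detection bias" and conclude that a placebo would add nothing. The detection half is justified only by the blinded central reading of the primary outcome. The same section says that patients are blinded because they are not told their arm, that urologists and anesthesiologists are not blinded, and that "randomization will be performed either by the urologist or the anesthesiologist or by a nurse". Whether ward nurses and clinical research assistants (CRAs) know the arm is not stated.
- **Interventions.** "the anesthetist or the anesthetist’s nurse will inject the experimental treatment". The furosemide prescription is issued through the e-CRF after randomization.
- **Participant timeline.** Anesthetic nurses monitor the patient in the recovery room. On pain: "Evaluation of pain will also be assessed by nurses during hospitalization", using a 0 to 10 scale at three time points. Patients self-assess for UTI in a follow-up book. A general practitioner or urologist then separates true infection from ordinary postoperative symptoms, and urine culture is done only if one of them asks for it. All adverse events since the operation are collected.
- **Safety.** Adverse events are self-declared in a logbook and also asked about by investigators. The one-month CRA call is described as a check on how furosemide was tolerated, on UTI and on other events.
- **Statistical analysis of secondary outcomes.** UTI and opioid use are compared between arms by the method used for the primary outcome. For safety: "Analysis of the occurrence of furosemide-related events will be descriptive".

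**The concern.** The conclusion is wider than its reasons. Blinded reading of a scan protects the reading of that scan. It says nothing about outcomes that depend on a clinician's judgement or decision, and here some of those clinicians know the arm.

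This matters most for UTI. It is the first secondary objective listed and it is directional: the trial sets out to show a lower rate with furosemide. An unblinded urologist who shares that expectation may, without intending to, order fewer cultures or read borderline symptoms as ordinary healing in the furosemide arm.

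The performance-bias reason is also incomplete. One injection is a short intervention, but the urologist who knows the arm follows the patient for three months. The article's own Background describes alpha-blockers as expulsive treatment, and the trial plans to examine their effect on the stone-free rate. A co-treatment that the authors think may change the primary outcome cannot be set aside as a source of bias because the study drug is given once.

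For safety, an analysis confined to events called furosemide-related may give no comparison between arms, depending on what the term means.

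**Working it through.** **1. The plan's own figure.** From Sample size: 85% versus 95%, two-sided 5%, power 90%, 1:1. With pooled variance under the null:

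n per arm = [1.960 × √(2 × 0.90 × 0.10) + 1.282 × √(0.85 × 0.15 + 0.95 × 0.05)]² / 0.10² = [0.8315 + 0.5361]² / 0.01 ≈ 187.05.

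This is 188 per arm (376) when rounded up; the article's 374 is 187 per arm, where power is 90.0%. Inclusions: 374 / 0.90 = 415.6, so 416, as stated. The design figure reproduces, and the concern does not depend on it. It only supplies 187 per arm for step 3.

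**2. Who determines each outcome, and do they know the arm?**

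| Outcome | Determined by | Knowledge of the arm |
|---|---|---|
| Stone-free on CT | Two central radiologists | Blinded |
| UTI | Patient's book, then GP or urologist; culture at a doctor's request | Patient blinded by non-disclosure; urologist unblinded; GP not stated |
| Pain score | Patient's score, collected by nurses | Patient blinded; a nurse may have randomized or injected |
| Opioid use | Treating team | Anesthesiologists unblinded; other staff not stated |
| Adverse events | Patient logbook, investigator questioning, CRA call | Patient blinded; urologist unblinded; CRA not stated |

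The stated reason on detection bias covers the first row only.

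**3. What unequal ascertainment could do (illustration).** The documents give no UTI rate and no ascertainment rate. Assume the same true rate p in both arms, complete recording in controls, and a proportion s of cases recorded in the furosemide arm. Then p1 = p, p2 = s × p, and the apparent OR = [p2/(1 − p2)] / [p1/(1 − p1)]. The rejection rate is that of the two-sided 5% pooled z-test with 187 per arm.

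Worked case, p = 0.10 and s = 0.8:
- OR = (0.08/0.92)/(0.10/0.90) = 0.783.
- Null SE = √(0.09 × 0.91 × 2/187) = 0.0296, so the critical difference is 1.960 × 0.0296 = 0.0580.
- Actual SE = √[(0.10 × 0.90 + 0.08 × 0.92)/187] = 0.0296.
- Rejection = Φ[(0.02 − 0.0580)/0.0296] + Φ[(−0.02 − 0.0580)/0.0296] ≈ 0.104.

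| p | s = 0.9 | s = 0.8 | s = 0.7 |
|---|---|---|---|
| 5% | OR 0.895, 5.6% | OR 0.792, 7.5% | OR 0.689, 11.1% |
| 10% | OR 0.890, 6.3% | OR 0.783, 10.4% | OR 0.677, 18.0% |
| 15% | OR 0.884, 7.0% | OR 0.773, 13.6% | OR 0.665, 25.6% |

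There is no true effect in any cell. Blinded CT reading changes none of them.

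**4. The safety term.** Secondary outcomes names furosemide adverse events, and the analysis section names furosemide-related events. Neither defines the term. Two readings are open:
- *Causal attribution.* Staff who know the arm would attribute, and a control patient who received no furosemide could not contribute.
- *Event types known for the drug.* Controls can have these too, and a comparison is possible.

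On both readings, events classed as unrelated or of another type fall outside the stated analysis, although they are collected in both arms.

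**The case against.** The case on the other side has weight.

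- **Patients are stated to be blinded.** Pain is the patient's own score, adverse events are self-declared, and UTI begins with self-assessment. The general practitioner may not know the arm. A reader might infer that all these outcomes are open-label; the article does not support that. Non-disclosure without placebo is weaker than masking, and a call framed around furosemide tolerance could undo it, but no passage shows that patients learn their arm. Ampoule labels are also kept in the patient file ("send the original to the pharmacy, and keep a copy in the patient file"), but nothing shows that those scoring pain consult them.
- **The detection-bias reason already names the primary outcome, and omitting the placebo was a deliberate pragmatic choice.** Both are true, and nothing here asks for a placebo. The opening sentence is nevertheless unqualified, and the performance-bias half has no such limit.
- **Control patients need not have zero events.** A reader might infer a control count of zero by construction. That follows only under causal attribution, which the text does not establish.
- **A SAP that is not shown may contain a full adverse event table.** It may, so the absence of that table is not the point. The point is that the one safety analysis the article does state uses an undefined term.
- **Differential co-treatment is not shown.** The alpha-blocker is described as usual treatment, and its timing relative to randomization is not given. This stands: the argument is that a single injection does not exclude the bias, not that it will occur.

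**Conclusion.** The statement holds for detection bias on the centrally read CT outcome and should be confined to it. It does not hold for UTI, opioid use or investigator-elicited adverse events. Pain is less exposed because the patient gives the score. It would also be wrong to infer that the CT outcome is free of every bias: blinded reading does not address co-intervention by an unblinded urologist during follow-up.

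The safety point is an ambiguity. If furosemide-related means causal attribution, the stated analysis gives no between-arm comparison. If it means known event types, it gives a partial one.

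The size cannot be computed from the documents. The illustrated range (OR 0.895 to 0.665, false rejection 5.6% to 25.6%) rests entirely on assumed UTI rates of 5% to 15% and 10% to 30% fewer cases recorded with furosemide. It shows what is possible, not what is expected. The primary detection-bias safeguard is sound, so this is a change that should be made and not a flaw that undermines the trial.

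**What to change.** 1. In Blinding, restrict the statement to detection bias for the CT outcome and remove the blanket claim on performance bias. Describe UTI, opioid and adverse event results as patient-blinded but not assessor-blinded.
2. Where a site's organisation allows it without extra staff, have the one-month call made by a CRA who has no access to the allocation. Use one neutral script in both arms that does not mention furosemide. E-CRF access rights can help with this caller; they cannot mask nurses who were present when the drug was or was not given.
3. Define furosemide-related. Whatever the definition, tabulate all adverse events by arm regardless of attribution, with risk differences and 95% confidence intervals.
4. Report alpha-blocker use after randomization and further stone procedures by arm.

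The cost is more modest claims for the secondary outcomes, one extra safety table, a short report of co-interventions and some organisation of e-CRF access. Sample size, primary analysis and treatment are unchanged. Trial status reports that no patient had been included when the article was written, so at that point the call script could have applied from the first patient. The wording and tables can be settled at any time before the data are examined by arm.
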